##### Balance

Force platform data will be collected using Senxis Force Plate Software, and synchronized with muscle activation and kinematics data using an additional analog input. Force platform data will be lowpass filtered at 15 Hz using a 2nd order zero lag Butterworth filter (46). The analysis of force platform-related outcomes will be done using a homemade MATLAB routine. Collected data will be the displacement of the center of pressure (COP), which is the difference between the measurement of the maximum and minimum center of COP in anterior–posterior and medial-lateral. We will also collect the maximum velocities of center of gravity displacement in the two planes: Excursion of COP in anterior–posterior (A/P) and medial-lateral (M/L). Usually, COP excursion are used in ergonomic fields to assess postural outcome in a standing position. We choose to analyze excursion of COP during a task to understand the impact of fatigue on postural during a complex task. We choose to compare COP excursion in A/P and M/L and COP Velocities between the control and “Fatigue session.”

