### Outcome measurements

Table 1 provides a summary of the measures that will be collected and that will serve for analysis in this study.

**Table 1 tab1:** Summary of measures to be collected.

Outcome	Instrument	Time of measurement	Unit
Primary outcome			
Performance	Composite score of time to complete the task associated with quality assessment	SUTT task	0–900
Secondary outcomes			
Muscle activation	RMS static 10th percentile muscle activity	SUTT task	(%MVE)
	RMS Median 50th percentile muscle activity	SUTT task	(%MVE)
	RMS Peak 90th percentile muscle activity	SUTT task	(%MVE)
Muscular fatigue	MPF: Mean power frequency	SUTT task	Hz
Force platform	M/L COP excursion	LASTT, LASTTbis and SUTT task	Cm
	A/P COP excursion	LASTT, LASTTbis and SUTT task	Cm
	M/L COP velocity	LASTT, LASTTbis and SUTT task	Cm/s
	A/P COP velocity	LASTT, LASTTbis and SUTT task	Cm/s
Kinematics	Range of Motion in the 18 DoF		Degree (°)
	Coefficient of multiple correlation (CMC)	SUTT TASK	
Perceived workload	NASA-TLX (English)	Total of 6 items	0–120
	SURG-TLX (English)	Total of 6 items	0–120
Motivation	VAS	Pre-Task and post task	(0–10)
Physical strain	Borg CR-10 Scale: legs, back, neck, Right and left shoulders and right and left arms	Pre and post task	(0–10)
Physical fatigue	VAS	Pre and post test	(0–10)
Effort	VAS	Post test	(0–10)

A/P, Antero posterior; COP, Center of pressure; DoF, Degrees of freedom; M/L, Mediolateral; LASTT, Laparoscopic Skills Training and Testing; MPF, Median power frequency; MVE, maximal voluntary electrical activity; NASA-TLX, National Aeronautics and Space Administration Task Load Index; RMS, Root mean square; SUTT, Suturing and Knot Tying Training and Testing; VAS, Visual analogic scale.

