#### Primary outcome: performance during a surgical simulated task

Our primary outcome will be the performance and will be assessed by the amount of time and numbers and quality of the stitches done during the SUTT exercise. We expect a decrease in performance during the “fatigue” session.

The time to complete the task will be assessed (in seconds) for every LASTT, LASTTbis and SUTT exercises combined by a quality assessment of the task (numbers of stiches completed withing 15 min, quality of stiches and nod). Every stich must be done by entering and existing within the black dots. The number of threads passes through each point (between 0 and 10, one pass per point through each black dot). A correct stitch equal one point on a 0–5 scale (5 being the total number of stiches). A correct Knot is rated 2 points if completed correctly and solid. Absence of trauma on the dot is rated on a 0 to 2 scale. All quality scales and the time to complete the task will be added to a online scoring platform called +he Academy’s Online Scoring Platform to produce a composite score going to 0–900.

For data analysis, we will keep only the best time to complete the task among the 3 trials for LASTT and LASTTbis.

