##### Kinematics

For kinematics analysis, a motion capture system composed of seven cameras (Vicon Vero 2.2) will be used. We will record kinematics data for seven joints (Figure 3) with a total of 18 degrees of freedom. Three-dimensional position of the thorax, arms, forearms, hands will be considered during the movement using the kinematic model (47, 48). We will base our model on an existing model that has been used by our team in a movement analysis study performed on seamstresses (47). Twenty-nine spherical reflecting markers (4 mm in diameter) will be placed on anatomical landmark of upper limbs and thorax. Markers placements are visible in Figure 4 and details of the markers disposition are available in Supplementary material 1. For practical reasons related to the use of laparoscopic forceps and the limited fine motor skills in the fingers during laparoscopy, we will eliminate the distal markers located at the hands. Before each motion capture, we will perform a capture in a neutral posture, the arms slightly in abduction with a slight internal rotation at the shoulders (abduction <30°) (49). Ranges of motion of the different degrees of freedom and CMC will be extracted.

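### COP excursion and maximum COP velocity are extreme values over tasks of unequal length, so a slower session can look less stable with no change in sway

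*Protocol article*

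**What the plan says.** The Balance section defines COP displacement as the quantity "which is the difference between the measurement of the maximum and minimum center of COP", taken in each of the two horizontal directions. It continues: "We will also collect the maximum velocities of center of gravity displacement in the two planes". That sentence names the centre of gravity where Table 1 lists COP velocity; I read both as COP.

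The record is the task itself: "We choose to analyze excursion of COP during a task to understand the impact of fatigue on postural during a complex task". Table 1 gives the time of measurement for all four COP measures as "LASTT, LASTTbis and SUTT task". The comparison is between sessions: "We choose to compare COP excursion in A/P and M/L and COP Velocities between the control and" fatigue session. Statistical analysis assigns a multivariate analysis of variance to the excursions and maximum velocities and names no term for duration.

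On task length, Experimental procedures sets limits of 3 minutes for LASTT and LASTTbis and 15 minutes for SUTT. The primary outcome section scores completion time in seconds for every exercise. It also states the expected direction, "We expect a decrease in performance during the" fatigue session, and Statistical analysis identifies the primary outcome with SUTT completion time.

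For range of motion, the Kinematics section says only "Ranges of motion of the different degrees of freedom and CMC will be extracted". It gives no formula, and the time-of-measurement cell in Table 1 is empty.

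**The concern.** A maximum can only stay equal or increase as a record is extended, and a minimum can only stay equal or decrease. For two separate sessions with identical sway, the longer one therefore has the larger expected range and the larger expected peak velocity. Nothing about balance needs to have changed.

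The study's hypothesis makes unequal records likely: if fatigue slows completion, the fatigue record is longer. The Introduction treats instability on the force platform as a possible sign of fatigue, and the study aims include explaining a decline in performance by neuromechanical mechanisms. The artefact would thus appear when performance has declined, in the expected direction, and could be read as the mechanism.

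The EMG section offers a useful contrast: it summarises amplitude by the 10th, 50th and 90th percentiles, which are far less sensitive to record length. The COP measures have no such protection.

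**Working it through.** **The plan's own figure.** The protocol states none for the COP measures. Its only power statement (30 participants, *f* = 0.30, power 0.8, Wilcoxon signed-rank) is not about COP, and this point does not depend on it.

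**Inputs from the protocol.** Range and maximum velocity over the task (Balance); limits of 180 s and 900 s (Experimental procedures); 29 participants (Abstract); two-sided 5% level (Statistical analysis).

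**Assumed inputs, because the protocol gives none.** Completion times of 600 s against 720 or 900 s for SUTT, and 120 s against 150 or 180 s for LASTT, with the same contrast for every participant. Sway is a stationary first-order autoregressive signal with time constant 1, 5 or 20 s, smoothed at 0.3 s and sampled at 25 Hz, with the same variance and spectrum in both sessions. Extra within-person session variation is 0 or 20% (log SD). The test is a paired t-test on log ratios with n = 29, standing in for the planned multivariate analysis.

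**Step 1: simulated inflation and null rejection.** Ranges run over the three time constants and, for rejection, over the two levels of extra variation.

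| Records | Range | Max velocity | Rejection, range | Rejection, max velocity |
|---|---|---|---|---|
| 600 vs 720 s | +1.7% to +3.0% | +1.0% to +1.4% | 6–22% | 5–11% |
| 600 vs 900 s | +3.6% to +6.7% | +2.4% to +3.0% | 14–45% | 9–25% |
| 120 vs 150 s | +2.9% to +6.3% | +1.7% to +2.0% | 10–26% | 6–18% |
| 120 vs 180 s | +5.2% to +11.9% | +3.0% to +3.2% | 20–69% | 8–30% |
| 900 vs 900 s | 0% | 0% | – | – |

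**Step 2: closed-form check of the rejection rates for range.** The noncentrality is √29 × ln(1 + inflation) / √(2·CV² + s²). CV is the simulated coefficient of variation of the range in the shorter record (taken as equal in both), and s is the extra log SD. Rejection is then the two-sided noncentral t probability with 28 degrees of freedom.

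- Time constant 20 s, 600 vs 720 s, CV 0.130, s = 0: ln(1.030) = 0.0296; √2 × 0.130 = 0.184; 5.385 × 0.0296 / 0.184 = 0.87; rejection 13%. With s = 0.20 the noncentrality is 0.59 and rejection 9%.
- Same time constant, 600 vs 900 s, s = 0: ln(1.067) = 0.0649; noncentrality 1.90; rejection 45%. With s = 0.20: 1.29 and 24%.

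Over all three time constants (CV 0.080, 0.099, 0.130) the formula gives 7–13% at 600 vs 720 s and 13–45% at 600 vs 900 s. For LASTT (CV 0.111, 0.145, 0.206) it gives 9–19% at 120 vs 150 s and 18–52% at 120 vs 180 s. The simulated upper ends of 22%, 26% and 69% lie above the formula and should be taken as including simulation noise.

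**Step 3: candidate remedies in the same simulation.** Equal record lengths remove the inflation. Mean velocity changes by 0.1% or less in every unequal-length case. Whole-task SD is only partly protected: +0.1% to +1.6% at 600 vs 720 or 900 s, but up to +12% at 60 vs 90 s with a 20 s time constant.

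**The case against.** Several objections narrow the point.

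- **Longer fatigue sessions are inferred, not stated.** Expected performance combines time with the number and quality of stitches. Counting stitches finished within 15 minutes suggests that some participants will not finish. Anyone who reaches the limit in both sessions has equal records and no artefact. This stands, and it dilutes the average effect.
- **A reader might infer that range of motion suffers in the same way.** The document does not say so. No formula or window is given, ranges could be taken per movement, and range of motion is not a measure of stability.
- **A reader might infer that the artefact is as large as the effect the study can detect.** The document gives no detectable effect for COP. On a paired scale at 600 vs 900 s, without extra variation, the shift is 0.0354/0.113 = 0.31, 0.0402/0.140 = 0.29 and 0.0649/0.184 = 0.35 SD of the differences for time constants 1, 5 and 20 s. A two-sided signed-rank test with 29 pairs needs about 0.55 for 80% power (normal differences).
- **A reader might infer that duration and sway can never be separated.** They can: completion time is recorded, and the force signal is processed in the team's own MATLAB routine.
- **Epoch rules may belong in a fuller document.** That would excuse silence. Here the article fixes the outcome as an extreme value over the task, and that definition creates the dependence on duration.

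**Conclusion.** The point holds for COP excursion and maximum COP velocity. As defined, their comparison between sessions is biased whenever record lengths differ, and the bias makes the longer session look less stable. For SUTT the assumed scenarios put it at a few percent: about 2–3% or 4–7% for the range and 1–3% for maximum velocity. That is enough to raise false positives for the range above 5%, slightly to moderately at 600 vs 720 s and clearly at 600 vs 900 s. LASTT could be affected more if sway is slow. All sizes rest on assumed durations, sway time constants and session variation, and on every participant having the same contrast; the bias is zero when durations are equal.

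These are secondary outcomes and the primary comparison is untouched. The change should be made, but the trial's main conclusion does not depend on it. The documents do not support extending the point to range of motion as it stands.

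**What to change.** In the Balance section, define COP excursion and maximum velocity within epochs of one fixed length, the same in both sessions, and average them over the task; consecutive 60 s windows are one example. The window must be no longer than the shortest usable record, which matters most for LASTT and LASTTbis. With steady sway, the number of windows then affects precision but not the expected value.

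Alternatively, add a measure that does not depend on duration, such as mean COP velocity. Whole-task SD should not be relied on alone. Cutting both records to the shorter session's duration also equalises length, but it discards the end of the longer session, where fatigue within the task might show.

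For range of motion, state the definition. Apply the same common window only if it is taken as maximum minus minimum over the whole task.

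The cost is a change to the MATLAB routine, some reprocessing and, with some windows, a little unused data. Trial status says no analysis has begun, so the rule can be fixed before results are seen.

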##### Kinematics

For kinematics analysis, a motion capture system composed of seven cameras (Vicon Vero 2.2) will be used. We will record kinematics data for seven joints (Figure 3) with a total of 18 degrees of freedom. Three-dimensional position of the thorax, arms, forearms, hands will be considered during the movement using the kinematic model (47, 48). We will base our model on an existing model that has been used by our team in a movement analysis study performed on seamstresses (47). Twenty-nine spherical reflecting markers (4 mm in diameter) will be placed on anatomical landmark of upper limbs and thorax. Markers placements are visible in Figure 4 and details of the markers disposition are available in Supplementary material 1. For practical reasons related to the use of laparoscopic forceps and the limited fine motor skills in the fingers during laparoscopy, we will eliminate the distal markers located at the hands. Before each motion capture, we will perform a capture in a neutral posture, the arms slightly in abduction with a slight internal rotation at the shoulders (abduction <30°) (49). Ranges of motion of the different degrees of freedom and CMC will be extracted.

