Moreover, we know that fatigue can lead to vestibular disorders in an individual and affect balance. In the context of surgery or simply in the study of ergonomic risks, postural asymmetry emerges as one of the most significant risk factors (25, 26). The assessment of postural asymmetries or fatigue is possible through objective methods such as differences in muscle activation measured by surface electromyography (sEMG). This technique has been extensively used in laparoscopy settings as an objective measure of muscular fatigue (27–29), although it may not always be reliable in detecting fatigue (30, 31). Postural balance can be assessed using force platforms. Force platforms can capture deteriorated postural balance, or instability that may be indicative of fatigue. Concurrently, kinematics can be assessed using motion capture. Kinematic studies can offer insights into movement quality and changes in movement patterns induced by minimally invasive surgery-related fatigue. In previous kinematics studies among laparoscopic surgeons, they seem to experience extended periods of neck rotation and asymmetrical position in shoulders that could justify the prevalence of musculoskeletal disorders among them (32, 33).

Ergonomics and fatigue prevention during minimally invasive surgery should be a concern for surgeon trainees, as they seem to be more exposed, compared to experimented surgeons, to muscle workload and awkward postures that could stick for the rest of their career. They seem to experience greater fatigue suspectedly induced by less adapted postures such as a greater upper body flexion angle or greater shoulders extensions (34, 35). Higher muscle activity is found in unexperienced surgeons especially in lower back muscle and biceps.

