## Methods and analysis

### Study design

We will compare the fatigue outcomes during 1 h of laparoscopic box test training in the morning with the same session performed after a whole-day work. Our study will be based on a cross over model, each participant will be his own control. We will try to show if the fatigue induced by a full day of work leads to changes in surgeon’s performance, quality of movement including upper body posture, perceived workload, and surgeon’s motivation.

We will conduct a controlled cross over study, following the SPIRIT guidelines. Every participant will perform two separate experimental days: (i) the first one planned in the morning, i.e., without any work intervention before testing (control day), (ii) the second one planned at the end of a full workday (fatigue day). The experimental sessions will always be performed on different days. The order of the days will be randomized to control which participant completes the control day or fatigue day first. Each participant will be included for a period of 6 months. Approximately 6 months of recruitment will be required to reach the target sample size. 6 month is the time needing to collect participant’s information, to perform a test training session and randomized participant for the experimental days. Recruitment started in March 2023 and ended in September 2023. Data collection is planned to last until May 2024 and analysis until September 2024. The flow chart of our study is presented in Figure 1.

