#### Statistical analysis

The level of significance for all statistical analyses will be set at 0.05 under the bilateral hypothesis.

Our primary outcome represented by the time to complete the SUTT task will be analyzed using the Wilcoxon signed-rank test.

The normality of quantitative data will be assessed using a graphical method and a Shapiro test. The dimensional consistency of the subjective data will be calculated using Cronbach’s alpha coefficient. We employed a Type III ANOVA to analyze the EMG data, assessing the significant effects of both experimental sessions (i.e., control versus fatigue) while accounting for potential variations between muscles, thereby ensuring a robust evaluation of the factors influencing muscle activation patterns.

To study our secondary outcomes with the force platform, we will conduct a multivariate analysis of variance (ANOVA) as a protected procedure to test the statistical dependence of the COP excursions, maximum COP velocities.

In EMG’s we will conduct an ANOVA to test the statistical dependance of RMS and MPF.

In kinematics, to compare CMC and range of between the two sessions, a one-way ANOVA with post-hoc (Bonferroni) will be performed for each DoF.

All statistical tests will be performed using Jamovi version 2.3.28.

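### The named kinematic outcomes measure movement amplitude and repeatability, so a null result could not be read as unchanged upper-body posture

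*Protocol article*

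**What the plan says.** All references are to the protocol article.

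- **Target.** Study design lists what a full workday may change. Besides performance, the list includes "quality of movement including upper body posture, perceived workload, and surgeon’s motivation".
- **Rationale.** The Background describes posture problems in terms of where joints are held: long periods of neck rotation, asymmetrical shoulders and, in trainees, a "greater upper body flexion angle or greater shoulders extensions".
- **Recorded data.** Under Kinematics, "Three-dimensional position of the thorax, arms, forearms, hands will be considered during the movement using the kinematic model". A neutral-posture capture precedes each recording.
- **Outcomes.** The same section ends with "Ranges of motion of the different degrees of freedom and CMC will be extracted". Table 1 agrees: its kinematic rows are "Range of Motion in the 18 DoF" and CMC. No mean, median or percentile angle, time in a posture zone or asymmetry index is listed.
- **Analysis.** Statistical analysis plans, "to compare CMC and range of between the two sessions, a one-way ANOVA with post-hoc (Bonferroni) will be performed for each DoF".

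**The concern.** The target and the outcomes describe different properties of the same recording. Posture, as the Background uses the word, is the level of a joint angle and how long it is held. Range of motion is the distance between two extremes, and CMC is an index of how alike repeated waveforms are. A surgeon who works the whole end-of-day session more flexed, but moves with the same amplitude and regularity, would look unchanged on both.

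What is at stake is the interpretation of a null result. If range of motion and CMC do not differ between sessions, the report may say that posture held up over the workday, although held posture was never tested. A larger sample would not help, because the quantities themselves do not respond to a constant shift.

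**Working it through.** The plan gives no figure to reproduce, no CMC formula and no joint-angle data. The check is therefore algebra plus an illustration on assumed curves.

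**Definitions.** Let y(i,t) be a joint angle in cycle i at frame t.
- Range of motion = max(y) − min(y).
- CMC (the usual waveform form, assumed here) = √(1 − W/T). W is the variance of cycles about the mean curve at each frame, and T is the variance of all values about the grand mean.

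**Constant shift c in one session, by algebra.**
- Range: (max + c) − (min + c) = max − min. Unchanged.
- Per-session CMC: c is added to every value, to the mean curve and to the grand mean, so it cancels in W and in T. Unchanged.
- Pooled CMC over an unshifted session and a copy shifted by c: each value lies c/2 further from the pooled mean, in opposite directions in the two sessions. The cross terms sum to zero, so c enters W and T only as c²/4. CMC falls, but equally for +c and −c.

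**Illustration.** Assumed: 5 cycles of 101 frames, a sinusoid of amplitude 10° around 30°, plus smooth noise.

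| Held shift | Mean angle | Range of motion | CMC per session | CMC pooled over both sessions |
|---|---|---|---|---|
| 0° | 29.4° | 22.989° | 0.9657 | 0.970 |
| 5° | 34.4° | 22.989° | 0.9657 | 0.918 |
| 10° | 39.4° | 22.989° | 0.9657 | 0.797 |
| 20° | 49.4° | 22.989° | 0.9657 | 0.537 |
| 30° | 59.4° | 22.989° | 0.9657 | 0.338 |

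The planned test compares CMC between the two sessions. That implies one value per session, so the per-session column is the one that applies.

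**Drift from the first to the last cycle of a session.**

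| Total drift | Range per cycle | Range over whole session | CMC per session |
|---|---|---|---|
| 0° | 22.989° | 28.85° | 0.966 |
| 5° | 22.989° | 30.3° | 0.928 |
| 10° | 22.989° | 32.8° | 0.843 |
| 20° | 22.989° | 42.5° | 0.619 |

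A posture that changes during the task can therefore move whole-session range and CMC. It does so by adding spread, which happens whichever way the angle drifts.

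**Amplitude can even move against level.** Adding 10° to the second half of every cycle raises the average angle, yet range per cycle falls from 22.989° to 13.59°. In this example a smaller range goes with a larger average angle.

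**Other planned outcomes.** Balance defines centre-of-pressure excursion as maximum minus minimum, so a constant shift cancels there too, and it is a whole-body measure. The RMS percentiles under Muscle activation are levels, but of muscle load. The Borg ratings are perceived strain by body region. None of them is a joint position.

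**The case against.** The strongest defence has four parts.

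1. *Posture is a minor phrase.* It appears as a target once, in Study design. The study aims section does not name it, and the Background says kinematics is there for movement quality and movement patterns, which range and CMC do address. This stands as a limit on weight. It does not remove the mismatch, because the phrase names something the study will try to show.

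2. *Other outcomes can respond to posture.* Static RMS of trapezius, deltoid and erector spinae, and Borg ratings for neck, back and shoulders, may change when posture does. This stands in part: it would be wrong to say that nothing in the plan could react. These measures can also change with load or perceived strain at an unchanged posture.

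3. *Range and CMC are not always blind.* Drift, or pooling across sessions, moves them, and fatigue could plausibly build during a one-hour session. This stands. Complete insensitivity is shown only for a shift held throughout, with CMC computed per session.

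4. *Absolute angles have their own problems.* Markers are re-placed on another day, and Experimental procedures lets each participant choose table height, with no stated rule for keeping it the same. This stands and belongs in the fix.

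Three stronger readings are tempting but unsupported.
- A reader might infer that the posture question cannot be answered at all. The recordings and the neutral capture exist, and Trial status says no analysis has begun. The gap is in the named outcomes.
- A reader might infer that a trainee posture hypothesis fails with it. Subgroup analysis names muscular and mental fatigue only; the trainee posture remarks in the Background report earlier literature.
- A reader might infer that the tests would reject at exactly 5% under a pure shift. That is not guaranteed. A one-way ANOVA that ignores pairing would reject less often per test when a participant's sessions are positively correlated, and the chance of some rejection across 18 degrees of freedom is a different quantity.

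**Conclusion.** The point holds in a limited form. The plan names upper-body posture as something to compare, but fixes kinematic outcomes that describe amplitude and repeatability. For a posture held at a different angle throughout a session, range of motion is exactly unchanged whatever the size of the shift. So is CMC when computed per session, which the planned between-session comparison implies. Where the measures do respond, they do not tell a worse posture from a better one.

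The cancellation is algebraic and does not depend on the assumed curves. The sizes under drift and pooling do depend on them, and on the assumed CMC formula. The size of any real postural change is unknown.

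The consequence is that a null kinematic result could not be read as no change in posture. This touches a secondary outcome only; the primary SUTT performance analysis is unaffected. The change should be made, but the trial does not depend on it.

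**What to change.** Add one joint-angle level outcome to Table 1, Kinematics and Statistical analysis, taken from the existing SUTT recording:

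- the median angle, with 10th and 90th percentiles (the percentiles already planned for RMS);
- for a short named set of degrees of freedom, such as thorax flexion and lateral tilt, and right and left shoulder elevation or extension;
- referenced to the neutral capture, and compared within participant between the two sessions.

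State that CMC is computed per session. Keep range of motion and CMC, labelled as amplitude and repeatability outcomes. If no level outcome is added, remove upper-body posture from the targets in Study design.

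**Cost.** A few lines in the processing routine and the outcome table, with no new measurement. Because analysis had not begun at the time of writing, the outcome could still be fixed in advance.

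**Downsides.** Absolute angles are more sensitive than range of motion to marker re-placement between days; referencing to the neutral capture reduces this but may not remove it. They also depend on the chosen table height, which should be recorded or kept the same across a participant's two sessions. Where sessions are already complete and height was not recorded, that limitation should be reported.
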